###### Appendices

Appendix 1 Declaration of Helsinki.

Appendix 2 European (CPMP) Guidelines on Good Clinical Practice for Trials on Medicinal Products.

# Introduction

## 1.1 Summary of the Study

Title: A randomized, assessor blinded, clinical trial to confirm the efficacy of a CE marked class I Medical Device formulation in the treatment of head lice

**Chief Investigator:** [name]

**Estimated Study Start:** September 2010

**Estimated Study Finish:** January 2011

**Participants:** One hundred and twenty (120) evaluable participants will be recruited to the study, randomised between three groups and treated with two vairants of the same CE marked product 5% 1,2-octanediol lotions.

**Type:** Children (aged 6 months and over) and adults who, upon inspection, are found to have live head lice.

**Products:** KindaPed AF (5% 1,2-octanediol alcohol free lotion)

KindaPed (5% 1,2-octanediol lotion with 20% alcohol).

**Methods of Application:** KindaPed AF 5% 1,2-octanediol alcohol free lotion (2-2.5 hours) and KindaPed 5% 1,2-octanediol lotion: These products will be applied directly to dry hair. Sufficient product will be applied to saturate the hair and scalp. The product will be left in place for 2 hours (maximum 2.5 hours) before being removed with proprietary shampoo. The product will be reapplied at Day 7.

KindaPed AF 5% 1,2-octanediol alcohol free lotion (8 hours or overnight): This product will be applied directly to dry hair. Sufficient product will be applied to saturate the hair and scalp. The product will be left in place for a minimum of 8 hours, or left on overnight, before being removed with proprietary shampoo. The product will be reapplied at Day 7.

**Study Design:** This is a randomised, assessor blind clinical investigation designed to confirm efficacy in use and obtain further information about routine usage of two variants of the same CE marked class I Medical Device product with the same active principle in the control and elimination of head louse infestation.

Participants will be assessed at Day 0 (recruitment) and then treated. An investigator will apply the treatment. The same treatment will be reapplied on Day 7.

Participants will be assessed for the presence of live head lice on Days 1, 6, 9 and 14 (+/- 1 day). The assessors will be blind to the treatment group. Any lice found at assessments will be taped into the Case Record Form (CRF) for size analysis.

**Aims of the Study:** To obtain directly comparative information to show that KindaPed AF 5% 1,2-octanediol alcohol free lotion is equally effective in the eradication of head lice as KindaPed 1,2-octanediol lotion.

## 1.2 Rationale

Infestation with the human head louse (*Pediculus capitis*) has been at a high level within the European Union since the appearance of strains of head lice resistant to one or more of the currently available insecticidal products were first described (1, 2, 3). Families are aware of a resistance problem but have no way of knowing if the lice they are trying to eradicate are resistant to the product they are using. Many people have attempted alternative methods of treatment such as combing (4) but for the most hard pressed families (as described in reference 3) this frequently has a poor outcome with children suffering infestations for many months (5).

Given a choice, a majority of care givers would choose to use a safe and simple chemical treatment to eliminate infestation form their children. Various products have been introduced into the European market as class I Medical Devices based on their physical mode of action and their general safety profile.

KindaPed (5% 1,2-octanediol lotion) and KindaPed AF (5% 1,2-octanediol alcohol free lotion) are class I Medical Device preparations based upon a cosmetic moistening and spreading agent.

The original KindaPed (5% 1,2-octanediol lotion) was originally investigated in a large randomised controlled trial in 2007-08 in comparison with 0.5% malathion liquid. In this study KindaPed was shown to be significantly superior to malathion using applications times of 2-2.5 hours and 8 hours/overnight. However, the KindaPed preparation was formulated with 20% isopropanol, which it is believed was the cause of a number of mild adverse reactions on excoriated skin.

KindaPed AF (5% 1,2-octanediol alcohol free lotion) contains no alcohol and should not cause irritation even on excoriated skin. This clinical investigation is designed to confirm no loss of efficacy of Kindaped AF versus Kindaped.

Both 5% 1,2-octanediol lotion preparations are used with a repeat treatment applied after one week as recommended by The British National Formulary (BNF) for all currently available treatments.

## 1.3 Aims (Objectives)

1. To compare efficacy of KindaPed AF (5% 1,2-octanediol alcohol free lotion ) with KindaPed (5% octanediol lotion with 20% alcohol) for elimination of infestation with head lice.
2. To compare KindaPed AF (5% 1,2-octanediol alcohol free lotion ) with KindaPed (5% octanediol lotion with 20% alcohol) with regard to prevention of louse egg hatching (ovicidal action) by monitoring the presence/absence of juvenile stages of lice following the first and second treatments.
3. To compare KindaPed AF (5% 1,2-octanediol alcohol free lotion ) with KindaPed (5% octanediol lotion with 20% alcohol) To investigate 5% 1,2-octanediol alcohol free lotion foam with regard to safety and participant acceptability.

## Design in Brief

This is a randomised, controlled, assessor blind, study of two variants of the same class I Medical Device product for control of head louse infestation. One hundred and twenty (120) evaluable participants, minimum age 6 months^[[1]](#footnote-1)^, who upon examination are confirmed to have head lice and who fit the selection criteria (see section 2.1.2 and 2.1.3) will be recruited to the study.

At the first visit (Day 0), verbal consent will be obtained to check for the presence of live head lice using a fine-toothed plastic detection comb. After the preliminary assessment, participants can be enrolled to the study, provided they comply with the inclusion/exclusion criteria, and any further questions they may have are fully dealt with.

Participants (or their parents/guardians if they are aged below 16 years) will be asked to give written informed consent and sign a Consent Form before participation in the study. There will be a separate Assent Form for younger children capable of giving written assent. Children too young to give assent can be entered in the study on the consent of a parent/guardian. Assent Forms will be witnessed by the parent/guardian and signed by the Investigator. Consent will be sought for permission to inform the participant’s GP that their patient is taking part in the study. Other infested household members who are unable to participate in the study for any reason, e.g. not being available for the assigned follow up visits, will be offered a standard of care treatment (Hedrin 4% liquid gel) in order to reduce the risk of reinfestation of participants during the course of the study.

The Investigator will assign each participant a study number, this being the next available number allocated to that investigator from a randomised treatment allocation sequence. Participants will be divided between three groups as follows:

Group A: KindaPed AF (5% 1,2-octanediol alcohol free lotion ), applied for 2 hours (maximum 2.5 hours) before washing off using shampoo, with a repeat treatment one week later.

Group B: KindaPed AF (5% 1,2-octanediol alcohol free lotion ), applied for 8 hours (minimum) or overnight before washing off using shampoo, with a repeat treatment one week later.

Group C: KindaPed lotion (5% 1,2-octanediol lotion with 20% alcohol), applied for 2 hours (maximum 2.5 hours) before washing off using shampoo, with a repeat treatment one week later.

Participants will be treated at Day 0 and Day 7 (+/- 1 day). A member of the study team will apply the treatment on both occasions. Participants will be assessed on Days 1, 6, 9 and 14 (+/- 1 day at each assessment) by a different member of the study team. Any lice found at assessments will be taped into the participant’s CRF.

All adverse events will be monitored during the study (see sections 2.3.5 and 2.3.6) and all changes in concomitant illness and medication will be recorded (see section 2.3.4). A Completion/Withdrawal Form will be completed at the end of the study period.

# 2. Materials and Methods

## 2.1 Participant Selection

### Total Numbers of Participants and Study Duration

One hundred and twenty (120) evaluable participants will be recruited to the study, randomised between three groups. The duration of the study will be 15 days (+/- 1 day), Day 0 being the first treatment day, with 14 days follow up.

### 2.1.2 Inclusion Criteria

1. Children and adults aged 6 months^[[2]](#footnote-2)^ and over of both sexes with no upper age limit.
2. People who upon examination, are confirmed to have live head lice.
3. People who give written informed consent, or if the participant is under 16 years of age whose parent/guardian gives written informed consent to participate in the study.
4. People who will be available for follow up visits by study team members over the 14 days following first treatment.

### 2.1.3 Exclusion Criteria

1. People with a known sensitivity to any of the ingredients in KindaPed AF (5% 1,2-octanediol alcohol free lotion) or in KindaPed lotion (5% 1,2-octanediol lotion with 20% alcohol).
2. People with a secondary bacterial infection of the scalp (e.g. impetigo) or who have an active long term scalp condition (e.g. psoriasis of the scalp).
3. People who have been treated with other head lice products within the previous two weeks.
4. People who have bleached hair, or hair that has been permanently waved within the previous four weeks.
5. People who have been treated with the antibiotics Co-Trimoxazole or Trimethoprim within the previous four weeks, or who are currently taking such a course.
6. Pregnant or nursing mothers.
7. People who have participated in another clinical study within 1 month before entry to this study.
8. People who have already participated in this clinical study.

## 2.2 Clinical Supplies and Materials

### 2.2.1 Physical Forms of the Study Supplies

KindaPed AF (5% 1,2-octanediol alcohol free lotion):

Active: 1,2-octanediol 5%

Excipients: Polyethylene glycol 6, water.

KindaPed lotion (5% 1,2-octanediol lotion):

Active: 1,2-octanediol 5%

Excipients: Sodium dodecyl sulphate 0.64%, propan-2-ol (isopropanol) 20%, water.

### 2.2.2 Packaging and Labelling

###### Packaging:

###### The products will be packed in plastic foamer bottles with each container holding 100mL of material. The bottles will be made from high-density polyethylene (HDPE) with screw fit, finger pump foamer nozzles.

Labelling:

The bottles of test product used in the study will be numbered and weighed on calibrated scales before use. A clinical trial label will be affixed identifying the individual bottle number and a blank section will be provided for completion of participant number and initials. The product will be labelled with appropriate clinical trial labelling that will also state that it is “For Clinical Trial Use Only”.

### 2.2.3 Care of Supplies

All supplies used in the study must be maintained securely under the direct responsibility of the Chief Investigator or under that delegated by the Investigator.

All supplies shall be dispensed in accordance with the Investigator's direction and it is the Investigator's responsibility to ensure an accurate record of supplies issued and returned is maintained.

All supplies should be stored at room temperature, out of direct sunlight and protected from extremes of environmental conditions.

All supplies will be used only while participating in the study and returned to MEC at the end of the study for weighing before being returned to Thornton & Ross Ltd.

### 2.2.4 Study Materials

Thornton & Ross Ltd will supply all the clinical study materials required for the duration of the study. In addition, numbered CRFs will be supplied for each participant.

### 2.2.5 Compliance

All supplies used, partly used, or unused will be maintained for collection by the study monitor.

## 2.3 Procedures and Investigations

### 2.3.1 Treatment Regimen/Allocation

This is a randomised, controlled, comparative study of KindaPed AF (5% 1,2-octanediol alcohol free lotion) in comparison with KindaPed lotion (5% 1,2-octanediol lotion with 20% alcohol) in the treatment of head lice. Each participant who satisfies the inclusion/exclusion criteria and agrees to participate will be randomised to one of three groups. Two groups will be treated with KindaPed AF (5% 1,2-octanediol alcohol free lotion) but using different application times (2-2.5 hours or 8 hours/overnight), the third group will be treated with KindaPed lotion (5% 1,2-octanediol lotion with 20% alcohol).

### 2.3.2 Randomisation

The randomised treatment allocation code will be generated using the free online randomisation service provided at <http://www.randomization.com/>. The treatment allocation will be made in 11 balanced blocks of 12 treatments and the Seed number and date of randomisation will be recorded on the randomisation plan.

The treatment allocations will be prepared as sheets bearing the identification of the product to be used and instructions for application of the relevant product. The product identification/instruction sheets will be sealed in opaque envelopes numbered sequentially on the outside with the participant number taken from the randomisation schedule. Each envelope will be enclosed in a CRF prior to use. Each investigator delegated to enrol participants will allocate the numbered CRFs to participants in numerical sequence. However, where two or more investigators, each allocated separate blocks of numbers, enrol participants in parallel the overall numerical sequence will not follow chronologically.

Only after written informed consent has been obtained will the investigator allocate a study number and open the randomisation envelope for that number. The investigating team will keep a second batch of envelopes, and a copy of the randomisation code also in a sealed envelope, in case an adverse event, reaction, or any other emergency circumstance necessitates that the code be broken.

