2.3.3.2 Recruitment (Day 0)

Screening:

Each potential participant will be asked for permission to assess their hair to confirm the presence of live head lice. The assessment will be made by dry combing the hair with a plastic fine-toothed head louse detection comb. Lice found during the assessment will not be removed. Other family members who give their verbal permission can also be assessed for the presence of living lice and may join the study provided they meet the inclusion/exclusion criteria.

Details will be recorded of how many people share the place of residence with the participant. Details will also be recorded of the number of people assessed and found to have lice, the number assessed and found not to have lice and the number that were not assessed. The number of people enrolled in the study will also be recorded.

Consent/Assent:

Participants and/or parents/guardians will be asked if they understand the requirements of the study and if they have any further questions concerning it. Provided they still wish to enter the study and meet the inclusion/exclusion criteria for entry, the participant or parent/guardian (when the participant is below the age of 16) will read and sign the Consent Form. The Investigator will countersign the Consent Form.

A separate Assent Form will be available for those under the age of 16 provided they are capable of signing their name. The Investigator and the parent/guardian will countersign the Assent Forms.

Children too young to provide signed assent may be enrolled on the basis of parental consent.

Case Record Form completion:

Personal data allowing identification of an individual will not be recorded in the CRF. However, as there are no source medical documents (i.e. patient medical records) available to the investigators a Source Data Verification Sheet will be completed for each participant that will be maintained separately from all other study documentation. This Sheet will include information such as name, date of birth, address, and contact details for the General Practitioner.

The following information will be recorded in the CRF:

1. **Declaration of Receipt of Informed Consent**: Confirmation that informed consent and assent (where relevant) was obtained, that a copy of the consent has been given to the participant and/or parent/guardian and that the original will be retained.
2. **Identification**: Participant's study number and age.

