3. **Hair Characteristics**: Characteristics will be recorded of the participant’s hair:
   1. Length: closely cropped, above ears, ears to shoulders, below shoulders
   2. Thickness: fine, medium, thick
   3. Degree of curl: straight, wavy, slight curl, tight curl
   4. Type: dry, normal, greasy
4. **Head Lice Details**: When the participant was last treated for head lice (an exact date if treated within the previous four weeks), the treatment that was used and the outcome (success or failure). The severity of the current louse infestation will be assessed using the following scale:
   1. Light infestation: single louse found only after 5-6 combs of the hair
   2. Moderate infestation: single louse found on the first comb of the hair
   3. Heavy infestation: more than one louse found on the first comb of the hair
5. **Medication Current at Entry**: Any medication being taken along with the date the medication started the total dose and the reason for the medication.
6. **Medical History**: Medical history and any current illnesses will be recorded.
7. **Inclusion/Exclusion Criteria**: Confirmation that the participant meets the inclusion/exclusion criteria for entry into the study.

Randomisation:

The Investigator will carry a block of sequential numbered envelopes, which correspond to the randomisation numbers on the CRFs. Each envelope will contain a randomised treatment allocation. After consent has been received, the next sequential numbered envelope will be opened and the specified treatment allocated.

Treatment:

A member of the study team will apply the treatment to the participant and the participant number and participant initials will be added to the label of the bottle used. Any unused product will be retained and returned to so that the weight can be recorded and the amount of product used calculated.

The products will be applied in the following way:

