## 3.4 Statistical Methods

Sample Size Determination:

The study has been designed to confirm that KindaPed AF (5% 1,2-octanediol alcohol free lotion) has an essentially similar efficacy comparable to that of KindaPed lotion (5% 1,2-octanediol with 20% alcohol). It is not designed as a full equivalence study but is designed to be able to identify any significant differences between the treatments in pair wise comparisons.

This study is based upon the same sample size as that used in four previous studies of head louse treatments conducted on behalf of Thornton & Ross Ltd (CTMK06, CTMK08, CTMK09, and CTMK10) for basic comparative purposes and is estimated to provide adequate data for demonstration of effect. The actual sample size of 40 per group makes allowance for dropout. Comparison of the results from this study can be made with the results from those studies with respect to similarities of population demographics, and with previous studies of 1,2-octandiol lotion (CTEP01 and CTEP02) with respect to efficacy outcome and acceptability.

Interim analysis

It is proposed to conduct an interim analysis of treatment outcome only after enrolment and completion of sixty (60) participants (approximately 20 in each group). This analysis will be conducted blind of treatment allocation using outcome data entered into a spreadsheet which would then be overlaid with treatment allocation identified only as “a”, “b”, or “c”. This will enable the Sponsor to identify whether one treatment is performing exceptionally well or exceptionally poorly and allow them to make a decision in good time whether they wish to extend or to curtail any aspect of the study. The results of this analysis will be conveyed to the Sponsor in narrative form only.

Analytical Methods:

The primary endpoint is the frequency of cure tested using the "intention-to-treat" population in comparison with the body of data obtained during previous studies using overnight or 2-2.5 hour application times for the product. Secondary endpoints will be the frequency of ovicidal failure and of reinfestation and the numbers of lice seen at the different assessment times. Other endpoints will be the safety of the product and participant acceptance.

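### A single disclosed block size of 12, used in sequence by enrollers who see past allocations, lets up to about 11% of allocations be deduced in advance: concealment is weakened, not absent

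*Protocol*

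**What the plan says.** Protocol section 2.3.2 sets the block structure: "The treatment allocation will be made in 11 balanced blocks of 12 treatments". Design in Brief names three groups, so a balanced block holds four of each. The same section sets how numbers are used: "Each investigator delegated to enrol participants will allocate the numbered CRFs to participants in numerical sequence". It foresees parallel enrolment, "where two or more investigators, each allocated separate blocks of numbers, enrol participants in parallel".

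Section 2.3.3.2 adds: "The Investigator will carry a block of sequential numbered envelopes". The investigator who has obtained consent opens the next envelope, and the sheet inside identifies the product.

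The protocol has real safeguards. Envelopes are opaque, sealed and numbered, and are opened only after written consent. Under section 2.3.3.3, follow-up is done by a different team member from the one who applied the treatment.

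Several people in one home may be enrolled. Section 2.3.3.2 says that other family members found to have lice "may join the study provided they meet the inclusion/exclusion criteria". It does not say in what order they receive numbers. Hair characteristics and infestation severity are listed for recording ahead of the randomisation step.

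**The concern.** An envelope hides the next allocation only from someone who cannot work it out. Here the block size is constant and printed in the protocol, and the person who enrols next has seen what the earlier envelopes in the block contained. Towards the end of a block, that person can infer what is left by subtraction.

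Such knowledge matters only where the enroller also has a choice. The clearest case is a household with several eligible members, because the enroller decides who takes the next number. A heavily infested child, one with long hair, or one for whom an overnight application would be awkward could be matched to a particular group or kept from it. The groups would then differ before treatment, and blinded assessment on later days cannot undo that.

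Section 3.4 gives 40 per group, so one participant is 1/40 = 2.5 percentage points of a group's cure rate. The trial is meant to support a conclusion of essential similarity, so even a few steered allocations would be unwelcome.

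**Working it through.** **Inputs.** Block size 12 and 11 blocks (2.3.2); three groups (Design in Brief); 120 participants (section 2.1); 40 per group (3.4).

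**The plan's own arithmetic.** 12/3 = 4 per group per block. 11 × 12 = 132 numbers, 44 per group. 120/12 = 10 full blocks, 40 per group. These figures agree with each other. The block size is a choice, so there is no derived figure to reproduce.

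**Assumptions.** The enroller knows the block size, remembers every earlier allocation in the block, and works through whole randomisation blocks.

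**Formulas.** With *n* places left in a 4/4/4 block, the remaining allocations are a random subset of size *n* of the 12. Write C(a,b) for the number of ways to choose b from a.

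- Next allocation certain (all remaining places belong to one group): 3·C(4,n)/C(12,n).
- At least one group used up: [3·C(8,n) − 3·C(4,n)]/C(12,n).

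| Position | n left | Certain | A group ruled out | Best guess right |
|---|---|---|---|---|
| 1 | 12 | 0% | 0% | 33.3% |
| 8 | 5 | 0% | 168/792 = 21.2% | 49.7% |
| 9 | 4 | 3/495 = 0.6% | 207/495 = 41.8% | 55.2% |
| 10 | 3 | 12/220 = 5.5% | 156/220 = 70.9% | 58.8% |
| 11 | 2 | 18/66 = 27.3% | 100% | 63.6% |
| 12 | 1 | 100% | 100% | 100% |

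The last column is the exact success rate of always naming the group with most places left.

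**Totals per block.**

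- Certain: 0.006 + 0.055 + 0.273 + 1 = 1.33 of 12, or 11.1%. Over 10 blocks this is 13.3 of 120.
- A group ruled out: 0.6%, 3.0% and 9.1% at positions 5 to 7, plus the values in the table, sum to 3.47 of 12, or 28.9%. Over 10 blocks this is 34.7 of 120.
- Best guess right: 6.14 of 12, or 51.2%, against 33.3% by chance. Over 120 participants this is 61.4 correct against 40.
- Product only (alcohol-free or alcohol lotion, 8 to 4 in each block): certain for 2.04 of 12, or 17%.

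**Alternative block structures.** Fixed smaller blocks would be worse: the certain share is 14.3% for 9, 20.0% for 6 and 33.3% for 3. Randomly mixed sizes were simulated for lists of 132, with an optimal guesser who knows the possible sizes but not their order (800 lists for 12/15/18, 1,500 for 3/6/9).

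| Sizes | Certain | Best guess right |
|---|---|---|
| Fixed 12 (exact) | 11.1% | 51.2% |
| Mixed 3/6/9 | 3.8% | 55.3% |
| Mixed 12/15/18 | 1.6% | 49% |

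Larger mixed blocks remove most of the certainty but little of the guessing advantage. Small mixed blocks reduce certainty and make guessing easier.

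**The case against.** The strongest reply is that the protocol already uses a recognised method of concealment: opaque, sealed, sequentially numbered envelopes, used in order and opened only after consent. Twelve is also a large block for three groups. Even a perfect counter cannot deduce about 89% of allocations, and certainty is nil for the first eight places of every block. All of this stands. A reader might infer that concealment fails altogether, or that late allocations are generally predictable. The document does not support that reading: only the twelfth place is always known, and the eleventh in about one block in four.

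Second, 2.3.2 speaks of separate blocks of numbers and 2.3.3.2 of a block of envelopes. Neither says that these coincide with the randomisation blocks of 12. If they do not, an enroller who starts mid-block lacks part of the history. This stands too, and is why the figures are upper bounds.

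Third, nothing shows that any investigator has a motive to steer. The frequency of multi-member households is not given, and no bias in cure rate has been calculated. That is correct: the point concerns opportunity only.

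Fourth, hair characteristics and severity are recorded at entry, and section 3.4 allows stratified tests where baseline differences are important. This could reveal steering on those traits, although the text frames the comparison against previous studies. It would not reveal steering on whether a long application was convenient.

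None of these replies removes the mechanism. Opening after consent prevents reading ahead, but not subtraction or the choice of which consented relative takes the next number.

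**Conclusion.** The point holds as a weakness in concealment. Up to about 11% of allocations could be known in advance, up to about 29% could have a group ruled out, and the best guess could be right about 51% of the time instead of 33%. These upper bounds rest on a perfect tally, knowledge of the block size, and possession of whole randomisation blocks. The missing household numbering rule is what most plainly gives an enroller something to choose. The documents do not show that any allocation would be steered, and no size of bias can be claimed. The change is worth making because it is cheap before the first participant and cannot be made good afterwards.

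**What to change.** 1. Before the start, regenerate the list in randomly mixed larger block sizes, for example 12, 15 and 18. Avoid small mixes such as 3, 6 and 9, which raise best-guess success to about 55% for an enroller who knows the possible sizes.
2. Remove the block size from 2.3.2 and from everything the field team holds, and record it only on the sealed randomisation plan. Suggested wording: *The list will be generated in permuted blocks of randomly varying size; the sizes are recorded only on the sealed randomisation plan and are not disclosed to anyone who enrols participants.* The emergency copy of the code kept by the investigating team should stay sealed for the same reason.
3. Add a household rule: *Where more than one member of a household is eligible, all will be consented and listed in order of date of birth before the first envelope is opened, and numbers will be given in that order.*

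Having someone who does not enrol issue each allocation, without disclosing earlier ones, would return guessing to one in three. It needs more staff and is optional.

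The cost of the three changes is a new list and a short addition to 2.3.2. Group sizes may differ by a few if recruitment stops inside a block.
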